**2. Implementation (quantitative and qualitative)**					
	Evaluation of E-Cog platform: Number of practitioners invited to participate in the E-Cog training Number of practitioners agreeing to participate in E-Cog training Reasons for nonparticipation or participation Number of practitioners not agreeing to participate in E-Cog training Total number of attendees participating in all of the training modules Total number of attendees per session or module Semistructured interview (health care practitioners)	Preintervention During intervention		Health care practitioners and service users	
	Evaluation of factors influencing the implementation of the 2 digital interventions: E-Therapy Attitudes and Process Questionnaire—Therapist Version [62] Semistructured interview (service users and health care practitioners)	Postintervention (8-12 and 24-30 months after the 2 interventions are implemented)		Health care practitioners and service users	
	Sustainability: Program Sustainability Assessment Tool [63] Monitoring of the intervention offer after an effectiveness trial at each site	Postintervention		Health care practitioners and service users	

^a^CANTAB: Cambridge Neuropsychological Test Automated Battery.

^b^Denotes primary outcomes in the study.

^c^MMI: MUSIC Model of Academic Motivation Inventory.

^d^STQ: Satisfaction Therapy Questionnaire.

^e^ABCR: action-based cognitive remediation.

### Cognitive Health Interventions

Interventions will be delivered through a secure videoconference platform. Network-connected tablets will be provided as necessary for the trial duration. ABCR [27,64] sessions consist of computer-based cognitive training activities (Brain Training Pro; 60%), teaching of problem-solving strategies (20%), and transfer activities (20%). Transfer activities include discussing and role-playing how cognitive skills are applied in everyday life and teaching potential strategies for overcoming cognitive challenges. ABCR targets include processing speed, attention, memory, executive functions, and social cognition, which are all commonly impaired in psychosis [12]. ABCR will be delivered in 16 sessions lasting 1.5 hours each over an 8-week period. MCT targets cognitive biases and errors in judgment underlying delusions using the theoretical foundations of cognitive behavioral therapy [65]. Sessions consist of discussions and activities aimed at increasing participants’ awareness of distortions and expanding their current problem-solving strategies. MCT will be delivered in 12 sessions lasting 45-60 minutes each over 6 weeks.

Both interventions will be offered at all sites. Depending on the site, interventions will either be offered concurrently or in sequence. Intervention group allocation follows a personalized, participant-centered approach. Potential participants will meet individually with the research coordinator at their site, who will provide a comprehensive overview of both interventions. Together, they will collaboratively determine which intervention best aligns with the participant’s personal goals and preferences. To maximize participant benefit and engagement, individuals will have the opportunity to complete the alternative intervention after finishing their initial chosen intervention. This flexible approach ensures that participants can potentially benefit from both interventions.

To improve adherence, participants will be contacted prior to each session with reminders. If participants miss several sessions in a row, therapists or a research assistant will contact them to confirm their interest in continuing the intervention and discuss any barriers to their participation. If any adverse reactions occur during the trial, participant involvement in our study may be discontinued after a discussion with the research team. Finally, to improve and track treatment adherence, sessions will be audio recorded, and 2 sessions from each of the ABCR and MCT groups will be randomly selected for review by 2 experienced facilitators using the treatment integrity assessment tool.

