**1. Effectiveness (quantitative)**					
	Cognitive tests or tasks: Brief version of the CANTAB^a^ computerized battery (Intra-Extra Dimensional Set Shift, Stocking of Cambridge, and Spatial Working Memory)^b^ [42] Wechsler Memory Scale (Logical Memory Subscale)^b^ [43] Cognitive bias against disconfirmatory evidence story^b^ [44] Jumping to conclusions (Beads)^b^ [45] Subjective cognition: Subjective Scale to Investigate Cognition in Schizophrenia (Brief)^b^ [46] Cognitive Motivation Scaleb [47] Davos Assessment of Cognitive Biases Scale^b^ [48] Symptoms: Positive and Negative Syndrome Scale-6 [49] Brief Negative Symptom Scale [50] Psychotic Symptom Rating Scales [51] Psychosocial: Self-Esteem Rating Scale—Short Form [52] Overall Emotional and Social Loneliness Scale [53] Short Warwick-Edinburg Mental Well-Being Scale [54] Questionnaire About the Process of Recovery [55] Basic Psychological Need Satisfaction and Frustration Scale [56] Autonomous-Controlled Motivation for Intervention Questionnaire [57] Personal and Social Performance [58]	Preintervention Postintervention 3-month follow-up		Service users	
	Intervention: Health Care Climate Questionnaire [59] Autonomous-Controlled Motivation for Intervention Questionnaire [57] MMI^c^ Cognitive Training Questionnaire [60] Satisfaction With Therapy (STQ^d^) [61] Time spent on cognitive drill exercises (ABCR^e^) Last log in (iCog platform)	Midintervention		Service users	

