#### Data Analysis

Data related to the analysis of objective 1, focusing on clinical effectiveness, will be compared between both interventions. Primary and secondary outcomes will be compared between the 2 interventions, using one as the active control for the other. First, propensity score matching will be used to identify a subset of participants who will comprise the active control group that is equivalent to the intervention group on background variables (sociodemographic variables, illness duration, medication dosage, length and nature of prior treatment as well as subjective reports of cognitive capacity and cognitive biases). Then, Z-standardized outcome data will be compared between the groups with generalized linear mixed effect modeling techniques using R software. Factors of interest will include fixed time (pre, post, and follow-up), fixed treatment (ABCR and MCT), fixed time and treatment interaction (time*treatment), random site (CIUSSS de l’Ouest-de l’Ile de Montréal, the Royal’s Institute in Ottawa, Kingston Health Sciences Centre, Ontario Shores Centre for Mental Health Sciences in Toronto, and Vancouver Coastal Health), random intercepts (participants’ ID), and random slopes (participant*time). Age, illness duration, medication dosage, length, and nature of prior psychological treatment will also be included as fixed covariates. This procedure will be done twice, with the active control group subset using propensity score matching. This approach ensures that participants are not counted twice and is an integral part of the propensity score matching procedure. Statistically, performing the procedure twice helps to validate the robustness of the matching process without introducing bias, as each participant is only included once in each comparison. Specifically, the procedure will be as follows: (1) ABCR as the intervention and MCT as the active control and (2) MCT as the intervention and ABCR as the active control. Missing data pattern will be assessed for whether it is missing completely at random, missing at random, or not at random [73]. If data are missing at random, multiple imputation will be applied [74]; if data are missing not at random, then the robustness of the primary analyses will be evaluated through sensitivity analyses.

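### Participants may take the comparator intervention before the 3-month follow-up, and the planned model does nothing to separate those data, so the follow-up contrast can be diluted

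*Protocol article*

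**What the plan says.** All references are to the protocol article.

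- **Cognitive Health Interventions**, on access to both treatments: "individuals will have the opportunity to complete the alternative intervention after finishing their initial chosen intervention". The stated purpose is that "This flexible approach ensures that participants can potentially benefit from both interventions". No gap, and no wait until after follow-up, is given.
- **Same section**, on timing within a site: "Depending on the site, interventions will either be offered concurrently or in sequence".
- **Same section**, on duration: "ABCR will be delivered in 16 sessions lasting 1.5 hours each over an 8-week period" and "MCT will be delivered in 12 sessions lasting 45-60 minutes each over 6 weeks".
- **Table 1, effectiveness rows**: the primary outcomes are measured at "Preintervention Postintervention 3-month follow-up".
- **Data Analysis**: the model has "fixed time (pre, post, and follow-up), fixed treatment (ABCR and MCT") and their interaction, with random effects for site and participant. The covariates include earlier psychological treatment. Receipt of the second trial intervention is not named as a term, a category or a reason to exclude data.
- **Data Analysis**, on matching in both directions: "This approach ensures that participants are not counted twice". The section then narrows this: a person enters any given comparison a single time.

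**The concern.** Each intervention is the active control for the other. A participant who takes the alternative before follow-up therefore receives exactly the treatment that the analysis contrasts with the first one. This is an advertised feature of the design, not incidental non-adherence. Under a two-level treatment factor, such a person's follow-up score appears to count as information on one intervention alone. The arms would then be pulled together at follow-up, and a lasting difference could be missed or understated.

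A second, smaller gap concerns people who complete both courses. The article does not say which course is analysed. If a second course were used, its pre score would already carry the effect of the first treatment.

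**Working it through.** **1. Can a second course fit before follow-up?**
The article does not anchor the 3 months. I assume that they run from the end of the first course.
- Length of the window: 3 × 52.18 / 12 = 13.0 weeks.
- Second course ABCR (8 weeks): 13 − 8 = 5. It is finished by follow-up if it starts within about 5 weeks.
- Second course MCT (6 weeks): 13 − 6 = 7. It is finished by follow-up if it starts within about 7 weeks.

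Overlap is therefore possible on the article's own durations. A later start would still put part of a course before follow-up.

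**2. What does crossover do to the follow-up contrast?**
Let d be the difference at follow-up on an intervention's target outcome if nobody crosses over. Let a share p of the comparator arm complete that intervention and gain its full effect. The comparator mean rises by p × d, so

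contrast = d − p × d = d(1 − p).

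If those who cross gain only a fraction g of the effect, the contrast is d(1 − pg), which is a smaller loss. The sample size needed to keep the same power for this contrast rises by 1/(1 − p)².

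Inputs: 0.50 for CR and 0.27 for MCT, from the Power section. The values of p are assumed, because the article gives none.

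| assumed p | 0.50 becomes | 0.27 becomes | sample size factor |
|---|---|---|---|
| 0% | 0.50 | 0.27 | 1.00 |
| 10% | 0.45 | 0.243 | 1.23 |
| 25% | 0.375 | 0.203 | 1.78 |
| 50% | 0.25 | 0.135 | 4.00 |

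**3. Power, as an illustration only.**
Take a comparison at follow-up alone, with the 300 of the Power section split as 150 per arm, two-sided alpha 0.05, SD 1 and no baseline adjustment. The split, alpha and SD are my assumptions.
- For 0.50, power is 99%, 97%, 90% and 58% at p = 0, 10, 25 and 50%.
- For 0.27, power is 65%, 56%, 42% and 21% (21.5%) at the same values.

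This is not the planned mixed model. Baseline adjustment would raise the levels: for 0.27 at p = 0, power is 69% to 91% at assumed correlations of 0.3 to 0.7. It would not undo the shrinkage. The article's own simulation result (300 participants, power up to 90%) cannot be reproduced from the inputs given, and this point does not depend on it.

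**4. Which part of the planned test is exposed?**
With time read as three levels and treatment as two, the interaction has (3 − 1)(2 − 1) = 2 degrees of freedom: one contrast to post and one to follow-up. For a first course, a second intervention begun after the post assessment cannot affect the first contrast. It can shrink the second, and so dilute the joint test.

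**5. Does the assurance about counting settle which course is used?**
One entry per person per comparison keeps a person out of both arms of that comparison. It does not say whether the entry is the first or the second course, or whether the other of the two matched analyses could use the other course.

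**The case against.** The strongest reply has four parts.

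- **Timing and uptake are unknown.** The text says after finishing, not immediately after. Delivery is in groups, some sites run the two interventions in sequence, and the Abstract says that groups run annually. The wait may be long. This stands: the durations show that contamination can happen, not that it does.
- **The same person in both arms.** A reader might infer that one person can serve in both arms of a comparison. The article does not support that, because Data Analysis admits each person once per comparison. Appearing in both of the two matched analyses is the stated design. Only the question of which course counts remains open. If a second course were used, matching and adjustment on prior treatment might partly register the first, but they do nothing for treatment taken between post and follow-up.
- **Power.** A reader might take the power figures above as the trial's loss of power. They are not. They describe a follow-up-only comparison, whereas the plan uses three visits and leaves pre-to-post intact.
- **Estimand and level of detail.** This is a pragmatic trial in routine care, and other psychosocial treatment is allowed and recorded. Analysing follow-up whatever was taken later is a legitimate choice, and an article may leave crossover rules to a fuller document. This stands in part. It is why removing post-crossover data should not become the main analysis by default: participants choose whether to cross, so treating those data as missing at random is debatable. It does not answer the point that the article itself fixes the model, its time levels, its treatment factor and its covariates, and these do not fit the offer of both treatments.

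**Conclusion.** The point holds in a limited form. As written, the plan can give a diluted follow-up contrast, and through it a diluted three-visit time-by-treatment test, because the comparator is available before follow-up and the model ignores its receipt. The follow-up contrast falls to about (1 − p) of its size. This rests on the follow-up interval starting at the end of the first course, and on those who cross completing the second course and gaining its full effect. The share p is not in the article, so the actual loss cannot be stated. That follow-up data would be analysed under the first intervention's label is inferred from the two-level factor; the article does not state it. The pre-to-post contrast of a first course is sound on this point, provided that the post assessment precedes any second course. Separately, the sentence on double counting leaves open which course is analysed for people who take both.

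**What to change.** These are changes to the analysis and to record-keeping. They do not alter what participants are offered.

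1. Analyse only each participant's first intervention episode, under that intervention's label.
2. Make the pre-to-post time-by-treatment contrast the primary effectiveness test.
3. Record the start date of any alternative intervention, and report the number who crossed over before follow-up by arm.
4. Present the follow-up contrast as secondary in two versions: all data regardless of crossover, and data after crossover excluded. State the assumptions of each. The second needs missing at random given the modelled variables, which is open to doubt when participants choose to cross.
5. Amend the sentence on double counting to say that only the first episode enters any comparison.

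**Cost.** Some wording and one date per participant who crosses over. The follow-up contrast loses primary status, and the version without post-crossover data rests on fewer records.

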### Training Platform

E-Cog training platform [66] is a digital platform providing training certifications for ABCR and MCT interventions developed by our group following the analyze, design, develop, implement, and evaluate model for the design of digital learning platforms [67]. Each training certification includes three training modules: (1) impact of cognitive impairments in psychosis and an introduction to remediation strategies (2 hours), (2) technological tools for digital mental health (1 hour), and (3) theoretical foundations and practical delivery of ABCR (~9 hours) or MCT (~12 hours). After obtaining the training certification, mental health practitioners participate in weekly supervision by a dedicated experienced trainer using a secure videoconferencing software. Screenshots from the training platform can be found in the multimedia appendices (Multimedia Appendices 2-4).

### Involvement of Individuals With Lived Experience

Peer support workers have been involved at different stages of the project. The pilot study, which informed this study, involved 2 peer support workers in the project committee. In this study, our peer support worker has been providing continuous consultation, which has led to changes throughout the study (eg, adapting intervention materials). Our peer support worker will also be involved in the intervention groups and will be coconducting the service user qualitative interviews.

### Statistical Analysis

#### Power

Monte Carlo simulations computed in R (R Foundation for Statistical Computing) were used to estimate the required sample size for our proposed models. Our analyses, based on simulated data, suggest that a total sample size of 300 provides enough statistical power (up to 90%) to detect anticipated effect sizes on primary outcomes of cognitive capacity and cognitive bias based on values from our group and those reported in the literature (CR: *d*=0.50 and MCT: *g*=0.27) [9,20,27,31]. The attrition rate for our digital groups has been approximately 20%; we will nonetheless conservatively adjust for an attrition rate of 30%. When considering the propensity score, this results in a requirement of 390 participants. Comparable studies using the same interventions and statistical methods in in-person settings have included similar sample sizes as those proposed at our individual sites [68,69]. Further, this sample size will allow us to detect anticipated effect sizes on secondary outcomes related to symptomatology (CR: *d*=0.28 and MCT: *g*=0.38) [70,71] and functioning (CR: *d*=0.36-0.51 and MCT: *d*=0.37) [31,71,72]. We also anticipate that the proposed sample size will be adequate to explore sex- and gender-related differences using subgroup analyses of 2 (male and female) and 4 (men, women, nonbinary, and other) groups, respectively.

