### Preliminary Work on Remote Delivery of Cognitive Health Interventions

Our preliminary work investigated the remote delivery of action-based cognitive remediation (ABCR) and MCT [26]. ABCR is a distinct form of CR, which integrates the traditional cognitive training techniques of CR with simulated workplace scenarios and goal setting [27]. This work involved evaluating 3 crucial early implementation outcomes: acceptability, appropriateness, and feasibility for both patients and therapists. Across 6 cohorts (3 ABCR and 3 MCT) conducted within Montreal, patients expressed high acceptability, with overall satisfaction for expectations and perception of progress. The interventions demonstrated feasibility; 36 participants completed therapy, attending an average of 10 MCT sessions and 12 ABCR sessions.

Using recently developed measures [28], therapists also reported excellent acceptability, appropriateness, and feasibility of the interventions [26]. Several facilitators and barriers to delivering these digital interventions were also identified. Barriers comprised patients’ clinical status (eg, more severe symptomatology and medication side effects), interaction issues (eg, lack of involvement and decreased accountability), technological challenges (eg, access to devices and the internet), program elements (eg, language options), and scheduling conflicts. On the other hand, facilitators included patients’ motivation to learn, therapist characteristics (eg, warmth and proper training), financial support for internet connectivity, program support (eg, education on interventions and ice breakers), and logistical adjustments (eg, offering evening sessions and forming smaller groups).

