## Results

A pilot pragmatic trial [26] has been conducted previously at the Montreal site, where 6 cohorts (3 ABCR and 3 MCT) were run, evaluating 3 early implementation outcomes: acceptability, feasibility, and engagement. Of the 28 participants attending at least 1 session, 21 completed more than half of the sessions. All completers reported a positive experience with therapy, 2 of 3 were not bothered by the remote setting, and 16 trusted the confidentiality of the information shared. Technology did not appear to significantly impede program participation. Therapist-rated levels of engagement were also satisfactory [26].

This study was approved by the institutional review board by September 2023. From September 2022 to January 2023 staff training was conducted across all 5 sites. Intervention materials including intervention manuals and digital portals began in June 2022 and continued until November 2023. Therapist training began on the E-Cog learning platform in April 2023 and is ongoing. All sites began recruitment in 2023 and have run cohorts of MCT and ABCR in their respective regions. Quantitative data collection occurs prior to and following the intervention group and is ongoing, qualitative data collection for implementation assessment began in summer 2024 and is ongoing. As of winter 2024, a total of 114 participants have been recruited and 32 therapists are enrolled in the E-Cog training platform with 25 therapists having completed the training. The updated project timeline can be accessed for those who create free accounts on the iCogCA Hub web page [77].

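### The 390 target is 300 × 1.3, so at the plan's own 30% attrition it leaves 273, not 300, and contains no allowance for propensity matching

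*Protocol article*

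**What the plan says.** The sample size reasoning is in the Power section of the protocol article. Its starting point, obtained by simulation, is that "a total sample size of 300 provides enough statistical power (up to 90%) to detect anticipated effect sizes on primary outcomes". The two anticipated effects are given as "CR: *d*=0.50 and MCT: *g*=0.27". On losses it says "The attrition rate for our digital groups has been approximately 20%; we will nonetheless conservatively adjust for an attrition rate of 30" per cent. It then concludes: "When considering the propensity score, this results in a requirement of 390 participants".

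The Abstract (about 390) and the Study Setting section (390) repeat this number as the recruitment target. The Data Analysis section explains why the propensity score bears on sample size: matching selects part of the sample as the comparison group, so some participants may go unused. The article states no matching loss, allocation ratio or significance level.

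**The concern.** The sentence says that 390 covers two separate losses, 30% attrition and whatever the propensity score step costs, and still leaves the 300 on which the power statement rests. Adding 30% to 300 does not undo a 30% loss, because the loss applies to the larger recruited number. If 390 is simply 300 plus 30%, it is short for attrition alone and holds nothing for matching.

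The target is the number the sites recruit to, and readers will judge a null result against the stated power. The cognitive bias outcomes carry the smaller anticipated effect and have the least room for a shortfall. A null finding there could be read as better supported than it is.

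**Working it through.** **Inputs from the article (Power section):** required number 300; attrition adjusted for 30%; attrition seen so far about 20%; target 390; effects 0.50 (cognition) and 0.27 (bias).

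**Assumptions, because the article gives no figure:** two-sided 5% test; equal arms; matching loss *m* shown over a range.

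**1. Reproducing 390.**
- 300 × (1 + 0.30) = 390, an exact match.
- 300 / (1 − 0.30) = 428.6, so 429.
- 300 × (1 + 0.20) = 360.
- 300 / (1 − 0.20) = 375.

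Of these four, only the first gives the stated figure. It uses up the whole increase from 300 to 390 on attrition.

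**2. What 390 leaves.**
- At 30% attrition: 390 × 0.70 = 273, which is 27 (9%) below 300.
- At 20% attrition: 390 × 0.80 = 312, which is 12 (4%) above 300.
- Break-even attrition with no matching loss: 1 − 300/390 = 23.1%.

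**3. What would be needed to end with 300.** The formula is 300 / [0.70 × (1 − *m*)], rounded up.

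| Assumed matching loss *m* | Recruits needed | Left from 390 at 30% attrition |
|---|---|---|
| 0% | 429 | 273 |
| 10% | 477 | 245.7 |
| 20% | 536 | 218.4 |
| 30% | 613 | 191.1 |

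**4. Effect on power.** Suppose power is 90% at 300. The noncentrality is then 1.960 + 1.282 = 3.242, and it scales with the square root of the sample size: power(N) = Φ(3.242 × √(N/300) − 1.960).
- N = 273: Φ(3.242 × 0.954 − 1.960) = Φ(1.13) = 87%.
- N = 245.7: Φ(0.97) = 83%.
- N = 218.4: Φ(0.81) = 79%.
- N = 191.1: Φ(0.63) = 73%.

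**5. Which outcome is exposed.** For an effect of 0.50 in a simple two-group comparison, power is Φ(0.50 × √(N/4) − 1.960). At N = 273 this is Φ(0.50 × 8.261 − 1.960) = Φ(2.17), about 98%. The larger effect has room to spare, so the shortfall matters for 0.27.

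**The case against.** **The loss from attrition is modest and conditional.** Starting from 90%, the fall at 273 is about 3 points, and if attrition stays at 20%, 312 remain. Both statements are correct and limit the harm. They do not rescue the sentence, which says it adjusts for 30% and also considers matching. A 4% margin at 20% attrition is little for a matching step after allocation by preference.

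**Thirty per cent might mean 30% of the completers.** Then 90 lost from 390 would be intended. That is an attrition rate of 23.1% in the usual sense, not a conservative 30%.

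**Dropouts are not wholly lost.** The Data Analysis section plans mixed models over three time points, and multiple imputation if data are missing at random. These may recover some information. The plan nevertheless chose to inflate for attrition, so they do not correct the inflation.

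**A stronger reading on power is tempting.** A reader might infer that the bias outcomes have far less power than stated, because a single-timepoint two-group comparison with an effect of 0.27 gives only about 65% at 300 and 61% at 273. The documents do not support that as the delivered power. The plan simulated its own longitudinal models, whose inputs an article may leave out. With baseline adjustment and an assumed pre-post correlation of 0.5, 0.6 or 0.7, the same normal approximation gives 77%, 83% or 91% at 300, and 73%, 80% or 88% at 273. The 90% figure is also worded as a ceiling.

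**The pilot counts do not belong here.** A reader might argue that true attrition is 25%, since "Of the 28 participants attending at least 1 session, 21 completed more than half of the sessions". That describes session completion, not missing outcome data. It also lies inside the 30% used and does not enter the 390. The statement elsewhere that "36 participants completed therapy, attending an average of 10 MCT sessions and 12 ABCR sessions" conflicts with 28 attendees, but this is a separate reporting discrepancy.

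**Conclusion.** The concern holds as arithmetic. At the attrition the plan says it adjusts for, 390 leaves 273, which is 27 below the required 300; retaining 300 needs 429 before matching. The claimed provision for the propensity score does not exist, and 390 suffices only if attrition is at most 23.1% and matching discards nobody.

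The size of the power loss is less certain. It is about 3 points (90% to 87%) from attrition alone, and more once matching discards participants, by an amount the article does not let anyone calculate. The 83%, 79% and 73% figures rest on assumed matching losses of 10%, 20% and 30%, a two-sided 5% test, and power of exactly 90% at 300. The point does not show that the cognitive bias outcomes are severely underpowered. It shows that the stated target does not support the stated power under the plan's own assumptions, and that the outcome with g = 0.27 bears the consequence.

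**What to change.** Correct the sentence in the Power section: 390 recruited leaves 273 at 30% attrition, and fewer after matching, whereas 300 would need 429 recruited before any matching loss. Remove the implication that 390 already provides for the propensity score.

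Rerun the existing simulation. In place of a single ceiling at 300, state the power for the cognition outcomes (d = 0.50) and the bias outcomes (g = 0.27) at 273 and over a range of matched sample sizes.

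The cost is one rerun of existing code and a few changed sentences. The target can stay at 390 and no extra enrolment is required. The downside is a less favourable power statement.
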